### Participant selection criteria

Patients aged 18 to 85 years who suffer SCA in the hospital caused by respiratory failure or hypovolemic shock and with a ROSC sustained for ≥ 20 min and met the following criteria at the same time are eligible to enrol in this study: Glasgow coma score ≤ 8 after ROSC, and before sedation (if any); the legal representative signed the informed consent; advanced cardiovascular life support is conducted. Those who meet the exclusion criteria (listed in Table 1) will not be enrolled in this study.

**Table 1 Tab1:** Inclusion and exclusion criteria

A. Inclusion criteria for observational part	
1. Cardiac arrest is caused by respiratory failure or hypovolemic shock;	
2. In-hospital cardiac arrest;	
3. Aged 18–85 years old;	
4. Patients with return of spontaneous circulation (ROSC) that is sustained for ≥ 20 min;	
5. Glasgow coma score ≤ 8 after ROSC, and before sedation (if any) ;	
6. The legal representative signed the informed consent;	
7. Advanced cardiovascular life support is conducted.	
B. Exclusion criteria	
1. No-flow time > 10 min (time from collapse to initiation of external cardiac massage);	
2. Low-flow time > 60 min (time from initiation of external cardiac massage to ROSC);	
3. Major hemodynamic instability (defined as a continuous epinephrine or norepinephrine infusion at a flow rate > 1 μg/kg/min);	
4. Cardiac arrest caused by advanced tumor and other end-of-state diseases;	
5. Cardiac arrest caused by an irreversible cause (such as severe trauma and poisoning);	
6. Cardiogenic cardiac arrest (acute infarction, malignant arrhythmia, heart failure, etc.);	
7. Acupoint with lesions, wounds, or skin diseases affects acupuncture;	
8. Allergic persons, or known to be allergic to treatment, such as metal;	
9. Pregnant or lactating women.	

Participants can withdraw from the trial for any reason at any time. Participants for whom, upon regaining consciousness (if any), the legal representative or patient requests study withdrawal may be removed from the study:

The flow chart of the study is presented in Fig. 1.

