### Randomization

Eligible patients enrolled in this trial will be randomly assigned to the EA or control groups in a 1:1 ratio. Randomization assignment will be carried out by a researcher ([name]) not involved in the treatment and assessment. This randomization will be run with a block randomization size of four by SPSS 17.0. The randomization block size will be concealed to guarantee rigorous methodology, and the allocation number will be sequentially assigned and stored. The unique code assigned to each newly eligible participant will be adequately preserved throughout this study. This procedure will ensure that each eligible patient could be assigned to either of the two groups with equal probability and that group assignment will not be influenced by the researchers. [name] and [name] will enrol and assign participants to interventions according to the preprepared allocation sequence. Considering that an included patient could withdraw from the study, their randomization number would be invalidated, so we will ultimately take the first 52–60 patients. Finally, the number of patients in these two groups may be different because of the actual procedures performed.

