### Data acquisition and biological parameter assessment

The recruited patients in this study will receive a participant ID, which will be labelled in the chart containing the personal information of the participants. Only investigators involved in this study will have the right to access the participant IDs on an as-needed basis.

The following data will be collected from all participants:Clinical, laboratory, and imaging-study findings on day 0, day 3, day 7, day 14, and day 28 (if available)Emergency medical service (EMS) record, ICU mortality, ICU length of stay, hospital mortality, hospital length of stay, 28-day all-cause mortality, and inpatient costDetails on the decision-making process

If patients are discharged early, investigators will call them back to the hospital as outpatients for free data acquisition and examinations.

The clinical parameters will include age, sex, cause of SCA, comorbidities, APACHE II scores, and SOFA scores. The EMS record contains the time of the call for EMS, the time of arrival, the initial cardiac rhythm, and management information. The data above will be collected on the day of enrolment and 28 days after registration. The schedule of the trial is shown in Fig. 2.

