### Statistical analysis

The data will be analysed statistically according to the method of a previous study [32]. Enrolled participants who cannot continue the study or follow up after treatment will remain in an “intention to treat” analysis. All statistical analyses will be performed with SPSS (version 17.0, Chicago, USA) for Windows by researchers not implementing the intervention. The analysis of this trial will be mainly descriptive focusing on estimation rather than hypothesis testing. All baseline outcomes will be summarized for each group using the appropriate descriptive statistics. No formal comparison of groups will take place. A full statistical analysis plan will be developed prior to the final analysis of the trial.

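### The rule that voids a withdrawn patient's randomisation number and enlarges intake to 52–60 conflicts with the stated intention-to-treat analysis and with the target of 50

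*Protocol article*

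**What the plan says.** All references are to the protocol article.

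- **Randomization:** 1:1 allocation in blocks of four. The section anticipates that "an included patient could withdraw from the study, their randomization number would be invalidated", and continues "so we will ultimately take the first 52–60 patients". It adds that "the number of patients in these two groups may be different because of the actual procedures performed". It also says that each participant's unique code will be preserved.
- **Statistical analysis:** "Enrolled participants who cannot continue the study or follow up after treatment will remain in an “intention to treat” analysis". The analysis is descriptive, without a formal comparison of groups.
- **Sample size determination:** 20 participants or more, and a plan to recruit 50 because 20% dropout is expected.
- **Outcome measures:** recruitment time is measured for 50 patients. Success requires a dropout rate of at most 20%. A favourable neurological outcome is CPC 1 or 2 at day 28.
- **Participant selection criteria:** entry requires a Glasgow coma score of 8 or less. Anyone may withdraw at any time, and "Participants for whom, upon regaining consciousness (if any), the legal representative or patient requests study withdrawal may be removed from the study".

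**The concern.** An analysis by intention to treat needs every randomised patient to keep the allocation and stay in the denominator. A rule that voids the number of a patient who leaves, and takes in more patients on that account, points the other way. Investigators who follow one rule literally will breach the other.

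No hypothesis test is planned, so neither type I error nor power is at stake. What is at stake is what the pilot is meant to deliver: outcome rates and an effect size for the main trial, and a retention figure judged against the 20% limit. Both depend on who stays in the numerator and denominator after withdrawal.

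Withdrawal may also be informative. Patients enter in coma, so those who wake are the likeliest to reach CPC 1 or 2, and waking is the only specific trigger the protocol names. Participants are not blinded, and only the EA arm has an added procedure, for up to 14 days, that an awake patient or a representative could refuse.

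**Working it through.** **1. The planned 50.** Inputs: 20 participants and 20% dropout (Sample size determination). Formula: N/(1 − d). If 20 is read as per arm, which the text does not state, then 2 × 20 = 40 and 40/(1 − 0.20) = 50, exactly the stated figure. Read as a total, 20/0.80 = 25, which does not reproduce it. On the per-arm reading, 50 already contains the dropout allowance.

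**2. The 52–60.** This is 2 to 10 above 50. The text ties the increase to voided numbers, so the same loss is allowed for a second time. The upper end equals 50 × 1.2, or 48/0.80; it does not follow from 40/0.80. No section reconciles the two targets.

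**3. Arm sizes.** With blocks of four from a single list, complete blocks give equal arms (52, 56 and 60 are all multiples of four), and one incomplete block can shift the arms by at most two. Incomplete blocks would be the ordinary explanation for unequal arms. The section instead gives the procedures performed as the reason, which does not sit well with analysis as allocated.

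**4. Effect on the dropout criterion.** Dropout = (randomised − valid)/randomised.

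| Randomised | Valid numbers | Dropout | Against the 20% limit |
|---|---|---|---|
| 52 | 50 | 2/52 = 3.8% | met |
| 60 | 50 | 10/60 = 16.7% | met |
| 52 | 40 | 12/52 = 23.1% | not met |
| 60 | 40 | 20/60 = 33.3% | not met |

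If voided numbers also left the count, every row would read 0%. The text does not say that they do; it does not exclude it either.

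**5. Effect on outcome rates (illustration).** The protocol gives neither withdrawal rates nor an expected CPC 1–2 rate, so these are assumptions. Let p be the true favourable rate, w the share of favourable patients removed and v the share of unfavourable patients removed. The observed rate is p(1 − w)/[p(1 − w) + (1 − p)(1 − v)].

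- p = 20%, w = 40%, v = 0: 0.12/(0.12 + 0.80) = 13.0%. In an arm of 25, this is 5/25 becoming 3/23.
- The same two patients replaced by others with a 20% favourable rate: (3 + 0.4)/25 = 13.6%.
- p = 35%, w = 40%, v = 0: 0.21/(0.21 + 0.65) = 24.4%.
- w = v = 20%: the rate is unchanged.
- Five unfavourable patients removed from an arm of 25 with 5 favourable: 5/20 = 25%.

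With no true effect, 40% removal of favourable patients in one arm only gives a false difference of about 7 points (p = 20%) to 11 points (p = 35%). Equal removal in both arms gives none. The sign depends on which arm loses patients and which patients they are.

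**The case against.** The strongest reply is that only the Statistical analysis section defines the analysis population, and it retains these patients. A voided number may simply be one that is not reused, and the same Randomization section preserves each participant's code. The trial is a descriptive pilot whose clinical results are to be treated as preliminary.

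Part of this stands. A reader might infer several things that the documents do not support:

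- **Deletion and replacement as rules.** The text neither says that a withdrawn patient's data are discarded nor that a new patient takes the vacated allocation. Both are inferences from the voiding and the larger intake.
- **An as-treated analysis.** The remark on procedures explains unequal group sizes; it does not assign patients to analysis groups.
- **Systematic removal of patients who wake.** Removal is permitted, on request, and the right to withdraw extends to everyone, including through representatives of patients who stay comatose. Being removed from the study is also not the same as being removed from the analysis.
- **Hidden dropouts.** The dropout rate is to be measured, and nothing says that voided numbers are left out of it.
- **A second outcome-related loss after discharge.** The plan says: "If patients are discharged early, investigators will call them back to the hospital as outpatients for free data acquisition and examinations". It does not make this the only route of assessment, and 28-day all-cause mortality is collected as well.

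The reply does not remove the conflict. If a voided number has no consequence for the analysis, there is no reason to enlarge the intake because of it. Pilot status does not help either, since retention and effect-size data are among the pilot's stated products. Nor can this be left to a later analysis plan: voiding numbers and extending intake happen during conduct.

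**Conclusion.** The point holds as a contradiction between stated rules, with a possible but unquantified bias. The voiding rule and the 52–60 intake cannot be squared with the intention-to-treat commitment or with the target of 50.

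If the voiding rule is followed, the reported outcome rates could be biased and the dropout criterion distorted. With 60 randomised and 40 valid numbers, dropout is 33.3% over all randomised, but 0% if voided numbers are left out. For outcomes, the fall from 20% to 13% assumes 25 per arm, 5 favourable patients and 2 of them lost from one arm only. It shows how sensitive a small arm is and does not predict a bias. The protocol supports neither a size nor a direction.

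**What to change.** - Delete the sentence that voids randomisation numbers, and the clause that attributes unequal groups to the procedures performed.
- State that every randomised patient keeps the number and is analysed in the allocated arm.
- Distinguish stopping EA from withdrawing from follow-up. Where consent permits, keep the data collected so far and obtain day-28 status from records.
- Count every withdrawal, by arm, in the dropout rate, with all randomised patients as the denominator.
- Reconcile 52–60 with 50, so that one recruitment target appears throughout.

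Recruitment is under way, so this should be settled by amendment before analysis. The cost is a few sentences and no extra patients. Some day-28 outcomes will be missing or less detailed, and the reported dropout rate may be less favourable.

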### Blinding and masking

Since this study involves acupuncture, it is challenging to achieve double blindness. However, to avoid bias in this process, the following specific measures are proposed:Participants will be recruited in strict accordance with the principle of randomization.The physicians participating in the outcome evaluation will be nonresearchers, making the trial efficacy evaluation blinded.The laboratory technicians and the biostatisticians will be blinded to the assigned treatments.

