**Methods:**

This is a prospective pilot, randomized controlled clinical trial. Eligible patients with PCAS after in-hospital cardiac arrest (IHCA) admitted to our department will be randomly allocated to the control group or the EA group. Both groups will receive standard therapy according to American Heart Association guidelines for cardiopulmonary resuscitation. However, the EA group will also receive acupuncture at the Baihui acupoint (GV20) and Zusanli acupoint (ST36) with EA stimulation for 30 min using a dense-dispersed wave at frequencies of 20 and 100 Hz, a current intensity of less than 10 mA, and a pulse width of 0.5 ms. EA treatment will be administered for up to 14 days (until either discharge or death). The primary endpoint is survival with a favourable neurological outcome. The secondary endpoints are neurological scores, cardiac function parameters, and other clinical parameters, including Sequential Organ Failure Assessment (SOFA) scores and Acute Physiology and Chronic Health Evaluation (APACHE) II scores, on days 0 to 28.

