### EA treatment

Disposable stainless steel acupuncture needles will be inserted at the Baihui acupoint (GV20, located at the intersection of the sagittal midline and the line linking the ears) and unilaterally on the side of the left leg at the Zusanli acupoint (ST36, situated on the front to one side of the leg, 3 *cun* below the acupoint ST35 and a cross-finger (middle finger) away from the leading edge of the tibia) to a depth of approximately 0.5 cm [28]. Furthermore, an EA instrument (Suzhou Medical Supplies Factory Co., Ltd., Jiangsu, China) will be connected to perform EA stimulation for 30 min using a dense-dispersed wave at frequencies of 20 and 100 Hz. The current intensity will be less than 10 mA (adjusted to induce a slight muscle twitch), and the pulse width will be 0.5 ms. One of the two electrodes of the EA stimulator will be connected to the needle at GV20, and the other electrode will be connected to the needle at ST36. This EA intervention will begin immediately after the ROSC for 20 min and will continue for up to 14 days, discharge, or death, whichever comes first. The EA will be performed by [name], [name], or [name], who will conduct the research and have previously received equal training.

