### Outcome measures

The primary feasibility outcomes are as follows:Evaluate the acceptability and compliance of EA in PCAS as an additional intervention of usual care.Explore the feasibility of recruiting, randomizing, and retaining participants.Evaluate outcome measures’ appropriateness.Collect data for effect size calculation in future sample size calculating.Develop an appropriate protocol for further study.

The length of time for recruitment of 50 eligible patients, recruitment rate and dropout rate will be measured. Successful recruitment is defined as at least half (50%) of eligible patients enrolled, with a dropout rate of no more than 20%.

The secondary patient-centred outcomes include the following:We define a favourable neurological outcome as a cerebral performance category (CPC) score of 1 or 2 on the 28th day after the ROSC. We define an ROSC as a spontaneous pulse and blood pressure, an abrupt sustained increase in end-tidal CO_2_ partial pressure (PETCO_2_) (typically ≥ 40 mmHg), or spontaneous arterial pressure waves with intra-arterial monitoring.Neurological scores: Glasgow Coma Scale (GCS) score, CPC score, modified Rankin Scale (mRS) score, and cranial computed tomography (CT) findings;Evaluation of cardiac function: troponin and lactic acid levels and echocardiography parameters.Sequential Organ Failure Assessment (SOFA) scoresAcute Physiology and Chronic Health Evaluation (APACHE) II scoresLength of stay in the ICU, length of hospital stay, hospital mortality/discharge, and hospital costsAdverse events

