Our decision to use an EA in PCAS is based on the results of our retrospective study published in Chinese, in which we found that EA attenuates the multiorgan failure of patients with PCAS [59], and those of a systematic review indicating that acupuncture ameliorates the injuries induced by experimental sepsis [60]. Whether EA is associated with mortality or a favourable neurological outcome after PACS is unclear. However, this trial is the first registered interventional and experimental study evaluating the potential benefits of EA on the neurological outcome of PCAS. The results of this trial might establish the importance of EA as a promising complementary strategy for the treatment of PCAS.

This study is the first study of EA for the treatment of SCA. The initial design was to consider SCA due to all causes; however, the ethics committee suggested that a pilot study in a focused area was needed to clarify the feasibility and safety of EA. The next step will be to expand the research. Therefore, there are several limitations to this trial. First, this is a pilot study with a small sample size and no blinding of the recruited participants. Second, the causes of SCA vary, and EA may be useful only for some causes of SCA, which could ultimately lead to bias; therefore, matched control and subgroup analyses are needed. Third, the treatment strategy received by ICU patients is highly complicated; therefore, the results of this trial might not be adequately explained solely by the therapeutic effect of EA. Fourth, as stated throughout this paper, this was a pilot study and no sample size calculation was performed; this was not powered for hypothesis testing of clinical outcomes. The clinical results will be treated as preliminary and interpreted with caution.

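### Using nonresearchers as outcome assessors does not by itself blind the CPC, mRS and GCS ratings

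*Protocol article*

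**What the plan says.** The Blinding and masking section concedes that "it is challenging to achieve double blindness" and then lists measures against bias. On outcome assessment it says: "The physicians participating in the outcome evaluation will be nonresearchers, making the trial efficacy evaluation blinded". The next item reads: "The laboratory technicians and the biostatisticians will be blinded to the assigned treatments". That direct statement covers laboratory staff and statisticians. For the outcome physicians, the only basis given for blinding is that they are not researchers.

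On the treatments, the abstract says: "Both groups will receive standard therapy according to American Heart Association guidelines for cardiopulmonary resuscitation". It continues: "However, the EA group will also receive acupuncture at the Baihui acupoint (GV20) and Zusanli acupoint (ST36) with EA stimulation for 30 min". No sham procedure is mentioned. The EA treatment section places needles at the scalp and the left leg, connects them to a stimulator, sets the current by a small muscle response, and says that treatment "will continue for up to 14 days, discharge, or death, whichever comes first". The Discussion lists "no blinding of the recruited participants" among the limitations.

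The Outcome measures section defines the favourable outcome as a "cerebral performance category (CPC) score of 1 or 2 on the 28th day after the ROSC" and also lists GCS, CPC and mRS scores. The section on data acquisition sets collection on days 0, 3, 7, 14 and 28. It has investigators bring early-discharged patients back as outpatients for examinations.

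**The concern.** The sentence gives a reason for blinding, and the reason does not support the conclusion. Independence concerns a rater's stake in the study. Blinding concerns what the rater knows about allocation. An intensive care physician who looks after the patient and sees the needles is a nonresearcher, so the rule as written would admit that physician as a blinded rater.

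CPC, mRS and GCS all call for clinical judgement, and the line between CPC 2 and CPC 3 decides whether a survivor counts as favourable. A rater who knows the arm and expects something of EA may place borderline patients differently in the two arms. Two statements give this weight even in a pilot. The abstract names survival with a favourable neurological outcome as the primary endpoint, and the Outcome measures section says that the data will feed the effect size for the main trial's sample size. The only blinding limitation in the Discussion concerns participants, so a reader would take the assessors' blinding as settled.

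**Working it through.** The plan gives no figure for this point, so the check is mainly a comparison of sections.

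**1. Does the stated rule conceal allocation?** Blinding and masking excludes researchers from outcome evaluation. The EA treatment section says that those who give EA also conduct the research, so the rule does exclude the people who deliver it. It does not exclude physicians who treat the patient, and it says nothing about what a rater may see or read.

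**2. Could a nonresearcher learn the arm?** Controls receive standard therapy with no sham mentioned. EA has visible needles at scalp and leg, a stimulator and a visible muscle response. Participants are not blinded. The setting is an emergency department and an intensive care unit. Allocation could therefore be known to clinical staff.

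**3. Which ratings are exposed?**

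| Rating day | EA period | Possible source of knowledge |
|---|---|---|
| 3, 7, 14 | may still be running | the procedure itself, charts, staff |
| 28 | ended by day 14 at the latest | charts, staff, patient or family |

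Death needs no judgement, so the exposure is confined to scores among survivors.

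**4. Who examines recalled patients?** The data-acquisition section has investigators recalling early-discharged patients for data collection and examinations. It does not say that a nonresearcher does the rating. These patients are survivors, the group in whom the CPC 2/3 boundary matters.

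**5. Scale of one rating.** Inputs: 50 participants and 20% dropout (Sample size determination) and 1:1 allocation (Randomization).
- Randomized per arm: 50 / 2 = 25. One re-rated patient: 1/25 = 4.0 percentage points.
- After 20% dropout: 50 × 0.80 = 40, or 20 per arm. One re-rated patient: 1/20 = 5.0 percentage points.

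**6. Illustrative range, on assumptions not in the documents.** Suppose a share s of EA patients are truly CPC 3 and a fraction q of them are rated up because the arm is known. The spurious difference is s × q.
- s = 5%, q = 10%: 0.05 × 0.10 = 0.5 points.
- s = 20%, q = 50%: 0.20 × 0.50 = 10 points.

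The Background cites mortality of 65–80%. If that applied here, 25 × 0.20 = 5 to 25 × 0.35 = 8.75 patients per arm would survive. An s of 20% is 5 of 25, which would be all survivors at the lower figure, so the top of the range is an extreme.

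**The case against.** The strongest reply is that the article does commit to blinded efficacy evaluation, and that the practical means of masking raters is detail which a condensed article may leave to the full protocol. This stands in part: the absence of a procedure is not itself an error. It does not rescue the sentence, which goes beyond omitting detail and gives a reason that does not establish blinding.

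A second reply is that nothing shows the outcome physicians to be treating physicians. A reader might infer that EA is given openly on the ward, that raters can read the EA notes, or that the trial will report blinding it does not have. The documents state none of this. They show that the rule permits an aware rater, not that one will be used.

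Third, needles are gone by day 28, so the visible procedure does not bear directly on the day-28 CPC rating. That is correct. What remains at day 28 is the indirect route through charts, staff, patient or family.

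Fourth, the consequence is limited. The Outcome measures section makes feasibility primary and clinical outcomes secondary, the Statistical analysis section plans description without formal comparison of groups, and the Discussion calls the clinical results preliminary. This lowers the stakes but does not remove them, given the abstract's primary endpoint and the planned use of the data for the main trial's effect size.

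**Conclusion.** The point holds in a limited form. The stated reason for calling the efficacy evaluation blinded is wrong, because nonresearcher status does not conceal allocation, and the recall of early-discharged patients by investigators is not reconciled with it. Rater-scored outcomes among survivors may be biased, most directly up to day 14 and indirectly at day 28.

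The firm part of the size is the step per patient: 4 points with 25 per arm, 5 points with 20. This assumes equal arms, the planned 50 participants and, for the second figure, that the 20% who drop out have no rating. The amount of actual bias cannot be derived from the documents. A reader might turn the step into an apparent effect, such as 7/25 (28%) against 5/25 (20%), but neither that base rate nor two generous ratings has any source in the plan. Nor do the documents support the conclusion that the ratings will be biased, or that mortality is affected. The point deserves correction but does not undermine the feasibility aims.

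**What to change.** Replace the sentence on outcome physicians. State that day-28 CPC and mRS are rated by one of the planned outcome physicians who had no part in that patient's care and has no access to the allocation or EA records, and that any unblinding is recorded. State that the same applies to patients recalled after early discharge, and amend the data-acquisition section to agree. Describe the day 3 to 14 ratings, and any other rating not done in this way, as independent but not blinded.

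The change leaves treatment, visits and sample size as they are. It costs some scheduling effort. If no planned outcome physician meets the condition for a given patient, the cost is a less favourable description of blinding. Whether enough such physicians exist at both sites is not stated in the article and should be confirmed.
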